### Recruitment

Each study site will feature a dedicated research coordinator (RC) who is a Certified Exercise Physiologist (CEP) or Registered Kinesiologist (RKin). Attending PC specialists (urologists, radiation oncologists, and medical oncologists) in PC clinics will identify potentially eligible patients and notify the RC. The RC will approach potential patients and a study information package will be provided. For patients interested in participating, written informed consent will be obtained and a baseline assessment will be scheduled. Based on patient volumes per centre and prior trial experience, we estimate recruiting 200 patients in approximately 24 months.

### Assessments

Participants will complete 5 assessments over the course of the trial (baseline, 3, 6 (end of intervention), 9, and 12 months). The 9- and 12-month assessments are completed following the end of the intervention and will provide information following the active intervention period. Outcome assessments are completed by a trained outcome assessor. Although neither the patient nor the exercise leader can be blinded to treatment allocation, outcome assessors will be blinded. At each assessment time point, participants will receive compensation to subsidize parking costs and to acknowledge their ongoing commitment to the trial.

### Baseline assessment

The baseline assessment consists of obtaining socio-demographic and clinical data as well as assessing fitness using measures of resting heart rate (HR), blood pressure (BP), oxygen saturation, body composition, upper and lower body strength testing, and a measure of functional endurance. Participants will also complete a series of questionnaires (to assess QOL, fatigue, and exercise adherence, including prior exercise program participation [114]) and will be scheduled to complete both a BMD test (if one has not been completed within the past year as per standard of care) and blood work. All measures are detailed below and summarized in Table 1. First aid and emergency equipment and supplies will be on hand for all testing and training sessions.

**Table 1 Tab1:** Summary of Study Measures at Specified Time Points

Domain/Measure	Time required	T_0_: (Baseline)	T_1_: (3 mo.)	T_2_:6 mo. (End Int.)	T_3_: 9 mo. (3 mo. f/u)	T_4_:12 mo. (6 mo. f/u)
Quality of life						
FACT-P	4–5 min	●	●	●	●	●
FACT-G	8–10 min	●	●	●	●	●
FACT-F (co-primary)	5 min	●	●	●	●	●
Physical Fitness						
6MWT (co-primary)	6 min	●	●	●	●	●
Sit-to-Stand Test	1 min	●	●	●	●	●
Grip Strength	1 min	●	●	●	●	●
Biological Outcomes^a^	< 5 min	●		●		●
Blood glucose						
Cholesterol profile						
PSA (safety)						
Testosterone^c^						
Haemoglobin (covariate)						
HbA1c (covariate)						
Body Composition						
Bone mineral density	30 min^b^	●				●
Body composition^d^	5 min	●		●		●
Adherence						
Accelerometer	–	●	●	●	●	●
GLTEQ	< 5 min	●	●	●	●	●
Sessional attendance^e^	–					
Adherence Predictor Variables						
HCCQ	5 min	●				
BREQ2	5 min	●		●		●
PNSF	5 min	●		●		●
PAB	5 min	●		●		●
Sedentary Behaviours	5 min	●		●		●
Cost-Effectiveness						
Health questionnaire	5 min	●	●	●	●	●
EQ-5D	5 min	●	●	●	●	●
Study Completion	5 min					●

^a^ All biological measures are considered to be standard of care at baseline and 12 months. PSA is considered to be standard of care at all 3 time points. Blood glucose, cholesterol profile, and haemoglobin tests at 6 months are NOT standard of care

^b^ Can be done on separate day to reduce participant burden

^c^ Will only be measured in participants who are not on continuous ADT for the duration of the intervention

^d^ Includes BIA, waist circumference, and waist circumference: height ratio

^e^ Only for those in supervised groups (done weekly)

*Abbreviations***:**
*6MWT* 6 min walk test, *BREQ2* Behavioral Regulations in Exercise Questionnaire – 2, *EQ-5D* EuroQol 5 dimensions of health scale, *FACT-G* Functional Assessment of Cancer Therapy General, *FACT-F* Fatigue subscale, *FACT-P* Prostate subscale, *GLTEQ* Godin Leisure Time Exercise Questionnaire, *HbA1c* glycated hemoglobin, *HCCQ* Health Care Climate Questionnaire, *Int* Intervention, *PAB* Planning, Attitudes, & Behaviour questionnaire, *PSA* prostate-specific antigen, *PNSF* Psychological Need Support and Frustration Scale – Relatedness Items

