Multiple studies have reported reductions in overall muscle mass, upper and lower extremity strength, grip strength, and daily functioning in men on ADT [12, 24, 29–36]. Two studies suggested an increased risk of falls in men on ADT, most of whom are elders [37, 38]. Numerous studies have also shown reductions in BMD within 6–12 months of ADT initiation, with further declines with ongoing ADT use for at least 10 years [39–46]. Loss of BMD has been associated with a 40–60% increased risk of fracture [13, 47–50]. Finally, ADT has also been associated with increased fat mass, insulin resistance, increased blood glucose, and unfavourable alterations in lipids [34, 35, 51–55]. These metabolic changes are associated with an increased risk of diabetes [13, 56–58] and cardiovascular outcomes [13, 56, 57, 59–63], although the latter remains controversial [64, 65].

Exercise-based interventions have been shown in at least 14 clinical trials to ameliorate most of these adverse effects [30, 66–77]. As summarized in several recent systematic reviews [78–82], the benefits of exercise have been shown in interventions of 8 to 24 weeks’ duration, including improved general or overall QOL [30, 70, 74], prostate-specific QOL [30, 74], and fatigue [30, 66, 69, 70, 73, 74]. Exercise has also been associated with improved muscular endurance (upper body = 22–115%, lower body = 23–167%), increased maximal strength (upper body = 40%; lower body = 96%), increased quadriceps muscle thickness by 16%, preserved or improved total body lean mass, and prevention of fat gain [30, 68, 70, 73]. No other intervention has been shown to improve as many side effects of ADT.

Three small studies found preliminary evidence of benefits of exercise in insulin parameters, glucose, lipids, or inflammatory markers, but effects on BMD remain unclear [73, 74, 83]. These effects need to be confirmed in larger studies, given the potential benefits of preventing diabetes or reducing cardiac risk factors in older men on ADT, the majority of whom will die of heart disease rather than PC [84–91]. Importantly, there is a robust literature in the general population showing that exercise improves glucose [92–94], lipids [95], and BMD [96–98]. And regular exercise after a diagnosis of PC may be associated with improved survival [99].

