### Study participants

The trial will include men with histologically confirmed PC who are fluent in English, able to provide consent, live close to a study centre and are either starting or continuing on ADT for at least 6 months or those in an androgen-deprived (or castrate) state for the duration of the intervention (total testosterone < 1.7 nmol/L). Men are ineligible if they are already meeting guidelines for moderate to vigorous physical activity (MVPA) or have conditions that would interfere with ability to participate. Details are listed in Additional file 2: Table S1.

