### Follow-up assessments

All follow-up assessments will include documentation of any change in clinical status as well as completion of the fitness measures described above and self-report questionnaires. BMD testing will occur only at baseline and 12 months and body composition measures and blood work will be collected at baseline, 6, and 12 months (Table 1).

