##### Body composition

Body fat percentage, fat-free mass, and fat mass will be measured using bioelectrical impedance analysis (BIA) with the Tanita TBF-300A device (Illinois, USA). Additional anthropometric measurements include waist circumference (WC), WC:hip ratio, and body mass index, following the standardized CSEP-PATH protocol [148]. In addition, BMD will be measured at lumbar spine, total hip, and femoral neck using dual x-ray absorptiometry (DXA).

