#### Secondary outcomes

Analyses for each of our secondary outcomes (QOL, fitness, biological, and body composition) will use mixed effects models for data at all time points incorporating within-person correlation. Within-person correlation of residuals will be handled by an autoregressive (AR1) error structure and factors will also be added for the 2 stratification variables (centre, ADT duration). All of these secondary outcomes will be analyzed as continuous variables after examining distributions to ensure symmetrical (approximately normal) distributions. Skewed data will be transformed as appropriate.

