#### Post-intervention period outcomes

Using similar mixed effects models, we will estimate changes over time and differences between exercise delivery groups in FACT-F and 6MWT during the 6-month post-intervention period, covering 3 assessment points (end of intervention, 3 months post-intervention, and 6 months post-intervention).

To give a quantitative overview of changes between and within groups over the entire 12 months, all study outcomes will be assessed using these same types of linear mixed effects models. By examination of estimated model parameters and their 95% confidence intervals, we can assess whether changes over time are similar between groups and whether differences between groups at any given time are clinically important.

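### A routine bone density scan up to a year old can serve as baseline, so the within-group 12-month BMD change can span 12 to 24 months and tends to overstate loss

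*Protocol article*

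**What the plan says.** In the protocol article, Baseline assessment, each participant is booked for a "BMD test (if one has not been completed within the past year as per standard of care". A man with a qualifying routine scan is not rescanned. Table 1 nevertheless marks bone mineral density at T0 without exception, so for him the existing scan has to stand as T0.

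Follow-up assessments gives the full schedule: "BMD testing will occur only at baseline and 12 months". BMD is a planned outcome at three sites; under Body composition, "BMD will be measured at lumbar spine, total hip, and femoral neck using dual x-ray absorptiometry (DXA".

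The analysis of secondary outcomes, which include body composition, "will use mixed effects models for data at all time points incorporating within-person correlation". Post-intervention period outcomes adds: "To give a quantitative overview of changes between and within groups over the entire 12 months, all study outcomes will be assessed" by the same kind of linear mixed model. The article mentions no scan date, no limit on scan age tighter than one year, and no adjustment for the interval between scans.

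Two further statements matter. Men are eligible if they "are either starting or continuing on ADT for at least 6 months", so some enter at or near the start of treatment. The Background reports "reductions in BMD within 6–12 months of ADT initiation", followed by continuing decline.

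**The concern.** The baseline rule and the description of the result do not fit together. One lets the first measurement lie anywhere in the year before baseline; the other describes change as if the clock started at baseline. For a man with a reused scan, bone change before randomisation is added to the trial year.

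The direction is predictable from the article's own Background. Men continuing ADT are expected to be losing bone, so the added period will usually add loss. In men who have just started, the reused scan may come from before ADT, and baseline then mixes bone measured off and on treatment.

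At stake is the descriptive within-group estimate of BMD change, and some precision in the comparison of arms. The Background says that the effect of exercise on BMD in these men is still unclear, so readers are likely to compare the reported change with other studies.

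**Working it through.** The plan has no figure for BMD to reproduce. Its only design figure, 81% power with 100 men per arm, concerns FACT-F and the 6-minute walk test. The check is therefore arithmetic on intervals.

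**Inputs from the article**
- Age of a reused baseline scan, a: 0 to 12 months (Baseline assessment).
- Follow-up scan: 12 months (Table 1; Follow-up assessments).
- Length of intervention: 6 months (Intervention).
- Randomisation follows the baseline assessment (Randomization). The gap between the two is taken as negligible.

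**Interval for one man**

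Interval T = 12 + a months. Share of T before baseline = a / T. Share of T covered by the intervention = 6 / T.

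| Scan age a (months) | Interval T (months) | T / 12 | Before baseline | Within the intervention |
|---|---|---|---|---|
| 0 | 12 | 1.00 | 0% | 50% |
| 3 | 15 | 1.25 | 20% | 40% |
| 6 | 18 | 1.50 | 33% | 33% |
| 12 | 24 | 2.00 | 50% | 25% |

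**Average over an arm**

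The article does not give the share of men with a reused scan, f, so a range is assumed. Reused scans are assumed to be spread evenly over 0 to 12 months, with mean age 6 and mean squared age 144 / 3 = 48. Then:

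- mean interval = 12 + 6f
- SD of the interval = √(48f − (6f)²)
- overstatement of mean loss, if loss is linear at one rate throughout = 6f / 12 = 0.5f

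| f (assumed) | Mean interval (months) | SD (months) | Overstatement |
|---|---|---|---|
| 25% | 13.5 | 3.12 | 12.5% |
| 50% | 15.0 | 3.87 | 25% |
| 75% | 16.5 | 3.97 | 37.5% |
| 100% | 18.0 | 3.46 | 50% |

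**If the rate before baseline differs**

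Let the rate before baseline be r times the rate afterwards. The overstatement becomes 0.5 × f × r. With f = 50%, r = 1 gives 25%, r = 0.5 gives 12.5%, and r = 0 gives none. A scan from before ADT may correspond to r below 1.

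**Scans that pre-date ADT**

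One randomisation stratum holds men with under 3 months of prior ADT. If that refers to a single current course, any reused scan in this stratum that is older than 3 months pre-dates ADT. With even scan ages (assumed), that is at least (12 − 3) / 12 = 75% of its reused scans.

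**Comparison of arms**

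Scan age is settled before randomisation and the one-year rule is the same in both arms. The expected mean of a is therefore equal between arms, and the extra loss cancels in expectation. What remains is variation in the interval between men (SD about 3 to 4 months above) and chance imbalance.

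**The case against.** The strongest objection is that the article never says how time is coded. It refers to data at the assessment time points and does not say whether BMD is modelled by nominal visit or by scan date. The sentence about the full 12 months is a general one covering every outcome. A condensed article may leave scan dating to the full protocol or analysis plan, neither of which is shown. This stands in part: coding by nominal visit is an inference, though the natural one. But the rule that admits a year-old scan as baseline and the description of change over 12 months are both stated here, and they disagree without any further document.

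A reader might infer that the comparison of home-based with group exercise is biased. The article does not support that. Scan age is fixed before randomisation, and prior ADT duration, which bears on whether a scan pre-dates ADT, is a stratification factor and is in the model.

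A reader might also infer that two years of loss will generally be reported as one. Twenty-four months is the extreme, and needs a scan a full year old; under even scan ages the mean for reused scans is 18 months. Loss before ADT concerns only men whose scan pre-dates treatment, and the article does not say how many there are.

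Finally, the percentages rest on assumptions, and linear loss is least credible where the scan pre-dates ADT. That is correct. They illustrate the size and do not predict it.

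**Conclusion.** The point holds as a limited one. As written, the plan mixes intervals of 12 to 24 months into a change described as 12-month, so the within-group BMD change includes a pre-randomisation part and tends to overstate loss. The illustrative 12.5% to 37.5% depends on three assumptions: reuse in 25% to 75% of men, even scan ages, and one steady rate of loss. It shrinks in proportion if bone loss before baseline was slower.

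The between-arm contrast loses some precision but is unbiased in expectation. BMD is a secondary outcome, so the co-primary analyses and the sample size do not change. This is a worthwhile small repair and does not threaten the trial's main conclusions.

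**What to change.** - Record the date of every baseline BMD scan, and report how scan age is distributed in each arm.
- Put time from baseline scan to randomisation into the BMD model as a covariate, or model BMD against actual scan time. If both scans are responses in a mixed model, the covariate must interact with time point, because a main effect alone would shift both scans equally and leave the change uncorrected. With scan age centred at zero, the change term then estimates change from a scan taken at randomisation.
- Add a sensitivity analysis limited to baseline scans taken close to randomisation and after ADT start, with the window fixed in advance.
- Do not label unadjusted change as 12-month change.

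Dividing each man's change by his scan interval should not be the main repair. It assumes steady loss, and where the scan pre-dates ADT it could average slower change off treatment with loss on treatment and so understate the latter.

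The cost is one data field, one added adjustment in the model, and a smaller sample in the sensitivity analysis. Sites already need the scan date to apply the one-year rule, and no additional scan is required.

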### Randomization

Patients will be allocated in a 1:1 ratio to treatment groups through a web-based central randomization scheme, with stratification on centre and prior duration of ADT (**<** 3 months vs. 3+ months). We are stratifying on duration of prior ADT as this has been shown to impact on subsequent declines in physical function and QOL as well as response to exercise [12, 115]. Randomization will occur following the baseline assessment. Once randomized, group-supervised participants will be scheduled to attend their first exercise session and home-based participants will be scheduled to attend an orientation session conducted by the RC and health coach. All participants will receive a study manual and basic exercise equipment (stability ball, mat, and resistance bands) to support program adherence.

### Follow-up assessments

All follow-up assessments will include documentation of any change in clinical status as well as completion of the fitness measures described above and self-report questionnaires. BMD testing will occur only at baseline and 12 months and body composition measures and blood work will be collected at baseline, 6, and 12 months (Table 1).

### Intervention

The 6-month intervention consists of two delivery arms, a group-supervised arm and a home-based arm. Both programs are designed with evidence from previous research by our team [30, 69, 70, 72, 76, 77, 116] and will be individualized using baseline fitness results. Prior to starting the intervention, the CEP/RKin will meet with participants to provide instruction regarding the exercise program. All participants will be asked to complete 4–5 days per week of mixed modality exercise incorporating flexibility (stretching for 5–10 min at the end of each session), aerobic exercise (approximately 30 min targeting 60–70% heart rate reserve (HR_reserve_) assessed by heart rate monitor), and resistance training (using body weight, resistance bands and/or free weights, a stability ball, and/or an exercise mat with prescribed exercises that target the major muscle groups), encouraging participants to work toward a target of 150 min per week as per established guidelines [117]. The absolute workload (60–70% HR_reserve_), and time is standard across all interventions. Program adaptation and progression are described below and summarized in Table 2.

**Table 2 Tab2:** Exercise Program Details

	Group-Supervised Exercise	Home-Based Exercise
Frequency of exercise	4–5 days per week (see also Delivery Location below)	
Intensity	AET: RPE of 11–14/20; HR of 60–70% of HRR RET: RPE of 11–14/20; 60–75% of 1RM × 8–12 repetitions × 2–3 sets; 5 exercises/session alternating each day (10 different RET exercises in total)^a^	
Session Duration	Identical	
Delivery Location of exercise		
*Facility-based*	3 x/week	Not applicable
*Home-based*	1–2 x/week	4–5 x/week
Trainer Presence	Group Exercise Leader	Unsupervised; remote support from health coach

*1RM* one-repetition maximum (maximum amount of weight that can be lifted), *AET* aerobic exercise training, *HRR* heart rate reserve, *RPE* Rating of perceived exertion, *RET* resistance exercise training

^a^All resistance exercises are conducted using body weight or resistance bands. A stability ball and yoga mat will also be available for use. RET exercises will target different major muscle groups delivered in two alternating programs. Day 1: Chest, upper back, shoulders, and arms. Day 2: Legs, gluteals, mid back, and core

Each program also includes an education component of 12 topics that focus on common concerns facing new exercisers (Table 3). Education sessions will occur during in-centre group classes for group-based participants and over the phone or during monthly in-person sessions for participants in the home-based arm of the intervention.

**Table 3 Tab3:** Education Topics

Education Topics	Key Points
1) Introduction to Exercise	● Benefits of Physical Activity ● Program targets 3 areas of PA (aerobic, resistance, and flexibility) ● PA is safe, feasible and has shown to provide benefits
2) Goal Setting	● Goal setting will assist with your dedication and motivation to complete the exercises ● SMART Goals - Specific, Measurable, Attainable, Realistic, Timely ● Use the goal worksheet in the manual ● Make long term and short term goals
3) Behavior Change	● The plan you set out may not be followed 100% ● Anticipate obstacles that may come as you are changing a behaviour and develop strategies for dealing with it before it arises. ● Monitor your progress, Reward yourself, Visualize your success
4) Planning for Barriers	● Biggest perceived obstacles ○ Lack of time, self-discipline, partner and ability ● Plan ahead for periods of inactivity
5) Social Support	● You are more likely to be successful if your family, friends and even co-workers are supportive of you ● Social support can occur in many forms – encouragement, completing activities with you, etc.
6) Monitoring Behavior	● Mix up your activities to stay motivated ● Try something new, or something you have done prev. ● It is very easy to enter an exercise rut
7) Maintaining Motivation	● Greatest source of motivation: Fun/enjoyment/stimulation, feeling of accomplishment, pleasure of learning and benefits (i.e. improved sleeping) ● Pursue something that you enjoy, that is convenient to your schedule. ● Take opportunities to be active
8) Personal Control	● Believing that you are in control of your own life give you reinforced motivation and further commitment to make changes
9) Self- Discipline, Reward & Attitude	● Self-discipline can result in increased productivity, improved self-esteem and confidence ● Rewards – use workbook in manual ● Attitudes toward change can determine whether you will be successful
10) Adapting your Program	● Adapting your program – FITT principle
11) Health and the Media	● Be mindful of the ‘Get fit quick’ media marketing – Healthy eating and regular PA will help maintain a long-term healthy lifestyle
12) Lifelong Active Living	● Use some of the tips and tricks in the manual to assist with continuing your active life. ● Change things up, work towards small goals, work with a friend, etc.

Group-based exercise program delivery will be standardized across sites using several approaches. Training staff (CEPs/RKins) will be required to attend an introductory training session covering participant testing and training parameters, safety precautions, and emergency procedures. An exercise manual will be developed for training staff outlining specific exercises and appropriate progression of intensity. Monthly conference calls will be held with CEPs/RKins and RCs across all sites to ensure standardization and solve problems. Finally, trainers will record weekly exercise plans and logs for each participant or group. These will be audited by the site PIs and randomly audited by the study PI and central RC monthly for the first 6 months and then every 3 months if compliance is > 90% with the training manual.

